### Study design

The study is a CRCT in each of the three countries. In each setting, 70 HFs are randomised to intervention or control (35 per arm). The intervention arm HF use the new PHISICC tools (substituting the usual HIS tools) and the control arm HF use the regular HIS tools. The trial is implemented in the real life contexts of HF carrying out their usual duties.

The trials started between the end of 2019 and beginning of 2020, depending on the country, when the intervention was installed and the baseline surveys carried out. Data collection will last until mid-2021.

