### Outcomes

There are five primary outcomes (table 2). Vaccination adherence is defined as the total number of vaccine doses given in the correct time interval to children in households in the HFs catchment villages over the total number of vaccine doses that should have been given during the same period. Antenatal care visits uptake will also be considered depending on the expected number of pregnancies in the study areas. Both are used as proxies for health outcomes in terms of protection against disease^13^ and prevention of pregnancy complications^14^ and are assessed in a random sample of households in the HFs catchment areas. Data concordance is defined as the level of agreement of HIS indicators between (1) records of healthcare events (recounts), (2) tallies (recounts) and (3) reports (aggregated data to higher levels of the system).^3^ Decision making will be assessed considering the diagnostics scope in the sick child (ie, number of different diagnoses per sick child consultation) and treatment appropriateness (ie, number of prescribed treatments that are supported by a documented diagnosis). These outcomes will be assessed in a random sample of records and corresponding reports during the last 4 months of the study period. HWs satisfaction will be assessed in all HWs in included HFs using a standardised questionnaire.^15–17^ While the intervention targets HF, some of the outcomes are measured at the level of HF and some others in the communities of HF catchment areas.

**Table 2 T2:** Outcomes and parameters used to estimate the sample sizes

	Outcome name	Subjects	Definition	Baseline estimate	Expected change	Comments
1	Vaccination adherence	Children under 1 year (sample of households in catchment areas)	Number of vaccines given in the previous calendar year over the number of vaccine due in the same period	75 given per 100 due	Increase of 10 per 100	Vaccines are clustered within children, and children within HFs
2	Data concordance	Recording tools in health facilities (samples of records)	Number of healthcare events (eg, vaccinations, antenatal care consultations) recounted in the previous calendar year vs the number of healthcare events reported in the same time period	Seven recounted for each 10 reported^3^	Increase of 1 recounted	A single estimate can be obtained in each HF or by time periods (no clustering)

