### Sample size calculations

The required sample sizes for each primary outcome were determined using simulation to incorporate the clustering (table 1) and to take the baseline and end-line surveys into account. Briefly, we simulated 1000 trials with variation between them caused by drawing different samples from the same distributions. We then used the regression models detailed in the data section to analyse each of the simulated trials and estimate the power as the proportion of trials which detected the effect of the intervention as significant. The simulation code was written in R (online supplemental files 2 and 3).

10.1136/bmjopen-2021-051823.supp2Supplementary data

10.1136/bmjopen-2021-051823.supp3Supplementary data

For each country, we require the probability of α, a type I error (rejecting the null hypothesis when it is actually true) to be less 0.05 and the power to be at least 80%.

For vaccination adherence, using a sample size of 35 HF per arm, we would have 80% power in each country to detect as significant a difference between a proportion of due vaccines given from 75% in the control to 85% in the intervention arms, assuming one child per household, 30 households per HF and a between-HF variation equivalent to a k of 0.25, where k is equal to the SD divided by the mean. The value of k is unknown, but was chosen in line with general observations by Hayes and Bennett.^20^

For data quality outcomes, with 35 HF per arm we would be able to detect as significant a difference from a ratio of 0.7 (reported:recorded) vaccinations in the control arm to 0.8 with the intervention with 80% power, assuming 100 recorded vaccinations per HF and an SD of 0.25 in the ratios between HF.

In terms of diagnostic scope, we would be able to detect an increase in the proportion of child visits with more than one diagnosis from 30% to 35% with 80% power with 35 HF per arm, 60 records per HF and assuming a k of 0.25.

We would be able to detect as significant an increase from 50% of treatments having a corresponding appropriate diagnosis to 60% with 80% power assuming 35 HF per arm, 1 treatment per child, 25 children per HF and variation between HF corresponding to k=0.25.

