### Data analysis

The analysis will be carried out for each country separately, and based on intention to treat.

Baseline population and health facility characteristics (ie, basic demographic characteristics of population and HWs, professional profile of HWs, health facility size and services) will be summarised. If large imbalances are observed at baseline, the variables can be used to adjust the effect estimate comparisons.^29 30^

The analyses vary for the different primary outcomes due to the unit of measurement and levels of clustering, the type of variable, and whether measurements were taken at baseline and endpoint or endpoint only. We use regression models to allow us to estimate the effect of the outcome while flexibly accounting for these issues and allowing adjustment for potential confounders.

Logistic regression will be used for the binary variables: vaccine adherence is measured by determining whether each vaccine due was received, and treatment appropriateness by whether each treatment was correctly prescribed. Data concordance and diagnostic scope are count variables and may be analysed with Poisson regression, depending on their distribution. The regression model for HW satisfaction will depend on how it is distributed.

The outcomes have different levels of clustering (children or consultations, HW, HF). We will account for these levels of clustering by including random effects in the regression models.

Four of the primary outcomes are measured at baseline and end-line. The effect of the intervention will be estimated using an interaction term between arm and survey in the regression models: that is, is the change in the outcome between baseline and follow-up in the intervention arm different to the change between baseline and follow-up in the control arm? The effect of HW satisfaction in Nigeria, measured only at end-line, will be estimated as the difference between the intervention and control arms.

All estimates for the effect of the intervention will be presented with 95% CIs. The analyses will be carried out using R.^31^

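### The listed random effects omit facility-by-survey variation, so the arm-by-survey effect may be given too small a standard error

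*Protocol article*

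**What the plan says.** The Data analysis section of the protocol article names the levels: "The outcomes have different levels of clustering (children or consultations, HW, HF"). It continues: "We will account for these levels of clustering by including random effects in the regression models". For the four primary outcomes measured twice, "The effect of the intervention will be estimated using an interaction term between arm and survey in the regression models". No term for HF-specific change between surveys is named. The random-effects structure is not written out, and no further term is ruled out.

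Table 2 (Outcomes) comments on data concordance: "A single estimate can be obtained in each HF or by time periods (no clustering"). The Sample size section nevertheless assumes an SD of 0.25 between HFs in that ratio.

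The same section requires, per country, a type I error probability "to be less 0.05 and the power to be at least 80" per cent. It says power was simulated with the regression models of the analysis section; the code is in online supplements.

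**The concern.** The surveys are repeated cross-sections. Vaccination is measured in children under 1 year, with baseline around the turn of 2019 to 2020 and end-line in mid-2021, so the children differ. Sick-child records also come from different periods. The HF is the sampling unit common to both surveys.

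An HF intercept cancels from a before-after contrast. What remains at cluster level is how much more or less one HF changes than another in its arm. A model with intercepts for HF and lower units treats that spread as zero. Lower-level effects are independent within an HF and cannot carry a facility-wide shift. In a logistic model the residual variance is fixed by the mean, so drift cannot enlarge the residual either. Identical change in every HF of an arm is hard to assume over a period in which, by the article's own account, the pandemic affected the conduct of the trials.

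At stake are confidence intervals that are too narrow and false-positive rates above the stated limit for up to three primary outcomes, and for concordance under some analyses.

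**Working it through.** **Inputs from the article.** c = 35 HFs per arm ("70 HFs are randomised to intervention or control (35 per arm"). Vaccination: "a difference between a proportion of due vaccines given from 75% in the control to 85% in the intervention arms", with "30 households per HF and a between-HF variation equivalent to a k of 0.25". Diagnostic scope: 30% to 35%, 60 records per HF, k = 0.25. Treatment appropriateness: 50% to 60%, 25 children per HF, k = 0.25. Concordance: 0.7 to 0.8, 100 records per HF, SD 0.25.

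**Assumed.** r, the correlation of an HF's effect between surveys, is not given; 1, 0.8 and 0.5 are used. One binary outcome per child and a two-sided test are also assumed.

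**Formulas**, with m records per HF per survey:
- between-HF variance B = (kp)²; within-HF variance W = p(1−p) − B
- variance of the interaction assumed by an intercept-only model: (4/c)(W/m)
- actual variance: (4/c)[W/m + (1−r)B]
- inflation V = 1 + m(1−r)B/W; type I error = 2[1 − Φ(1.96/√V)]

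**The plan's own figure first.** For power, W is taken at the control value in three of the four arm-survey cells and at the target value in the fourth. Vaccination at r = 1: W is 0.1523 at 75% and 0.0823 at 85%. The variance is (3 × 0.1523 + 0.0823)/(35 × 30) = 0.000514, SE 0.0227, and power Φ(0.10/0.0227 − 1.96) = 99%. The same steps give 71% for diagnostic scope and 87% for treatment. The stated 80% is not reproduced, but it came from simulation code that is not shown, so this is no evidence of an error.

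**Type I error at r = 0.8**
- Vaccination: B = 0.1875² = 0.03516, W = 0.15234. V = 1 + 30 × 0.2 × 0.2308 = 2.38; 1.96/1.544 = 1.269; type I error 20%.
- Treatment: B = 0.125² = 0.015625, W = 0.234375. V = 1 + 25 × 0.2 × 0.0667 = 1.33; type I error 9%.
- Diagnostic scope: B = 0.075² = 0.005625, W = 0.204375. V = 1 + 60 × 0.2 × 0.0275 = 1.33; type I error 9%.

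A simulation of 600 null trials per cell, fitting a logistic model with an HF intercept only, is shown in brackets.

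| Outcome | r = 1 | r = 0.8 | r = 0.5 |
|---|---|---|---|
| Vaccination adherence | 5% (4.3%) | 20% (22%) | 35% (34%) |
| Diagnostic scope | 5% (5.3%) | 9% (9.3%) | 15% (15%) |
| Treatment appropriateness | 5% (3.8%) | 9% (9.7%) | 15% (14%) |

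At r = 0.95 vaccination is still about 9%. At r = 0 the figures are 49% for vaccination and 23% for the other two. An HF-level change-score test on the same simulated trials gave about 3% to 7%.

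**Approximate power with the correct SE**, r = 1 / 0.8 / 0.5: vaccination 99% / 79% / 51%; diagnostic scope 71% / 59% / 46%; treatment 87% / 76% / 62%.

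**Concordance**
- One ratio per HF per survey: HF-by-survey variation falls in the residual, and ignoring the pairing makes the SE too large. Type I error is 2.8% if the two ratios correlate 0.2, and 0.6% at 0.5.
- T periods per HF per survey taken as independent, with period-level noise variance E: actual over assumed variance is [T(1−r)B + E]/(B + E). This exceeds 1 when T(1−r) > 1. With monthly periods over the calendar year in Table 2, 12 × 0.2 = 2.4, so the SE is too small at r = 0.8. Over the four months named in the Outcomes text, 4 × 0.2 = 0.8 is not enough, but 4 × 0.5 = 2 is.
- Poisson counts with no HF effect and no overdispersion: W/m = 0.7/100 = 0.007 and B = 0.25² = 0.0625. At r = 0.8, V = 1 + 0.2 × 0.0625/0.007 = 2.79 and type I error is 24%; at r = 0.5 it is 40%.

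**The case against.** The strongest reply is that the article never specifies an intercept-only model. It condenses a fuller plan, speaks of handling clustering flexibly, and puts its simulation code in supplements. A further random term may well be there. This stands to the extent that the inflation is a risk the text leaves open, not a demonstrated result. It does not remove the point: the article names particular levels, says random effects will account for those, and pairs them with an estimator whose main cluster-level error is not among them. An analyst following the text would leave it out.

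Three stronger readings are tempting, and the documents do not support them.
- A reader might take 9% to 20% as the trial's type I error. That is only the spread across three outcomes at an assumed correlation of 0.8. It also rests on k = 0.25, which the article itself calls unknown.
- A reader might infer that the stated power is overstated. Without the code this cannot be shown. For vaccination the stated 80% lies far below the intercept-only 99% and close to the 79% obtained with drift at r = 0.8.
- A reader might take the absence of clustering in Table 2 as wrong throughout. For one ratio per HF per survey, ignoring HF is conservative. Poisson regression is also only a possibility in the text, dependent on the distribution.

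**Conclusion.** The point holds conditionally. As written, the list of levels lacks HF-by-survey variation, although the effect is an arm-by-survey interaction from repeated cross-sections. If only the listed levels are fitted, type I error ranges from the nominal 5%, when every HF keeps its relative position, to the rates tabulated above. Vaccination adherence is the most exposed, and several doses per child would raise its inflation further for the same k, because the within-HF variance is smaller.

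The vaccination figures do not apply in Mozambique, where the household survey was cancelled. Satisfaction measured only at end-line has no interaction term and is unaffected. For concordance the risk is confined to several periods per HF treated as independent, once T(1−r) exceeds 1, and to Poisson counts with neither an HF effect nor overdispersion.

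**What to change.** - In the Data analysis section, add an HF-by-survey random effect nested in HF to every model that uses both surveys. Alternatively, analyse one end-line summary per HF adjusted for its baseline summary (70 observations per country).
- In Table 2, limit the no-clustering remark for concordance to one estimate per HF per survey, and say that several periods from one HF are repeated measures. If counts are modelled, include HF effects and overdispersion.
- Check whether the power simulation already contains HF-specific change, and restate power over a range of between-survey correlations.

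The cost is one variance term in the R models, wider confidence intervals and possibly less favourable stated power. The change can be made before the analysis code is fixed and the arms are disclosed.

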We already had the agreement of the MOH and selected HF compliant with the inclusion criteria were provided with the intervention shortly after completing the baseline data collection. Therefore, recruitment as such took place at the same time of the allocation of HF into intervention and control arms.

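### For the outcomes with a baseline, holding the randomised arms to a common baseline mean would estimate the effect more precisely than the planned difference in change, at the cost of one model term

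*Protocol article*

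**What the plan says.** The Data analysis section states that "Four of the primary outcomes are measured at baseline and end-line". For these, "The effect of the intervention will be estimated using an interaction term between arm and survey in the regression models", and the question is put as "is the change in the outcome between baseline and follow-up in the intervention arm different to the change" in the control arm. The baseline arm difference is therefore a free parameter, subtracted in full from the end-line difference. On clustering, the section says "We will account for these levels of clustering by including random effects in the regression models". The levels it lists are children or consultations, health workers and HFs. A random effect for HF by survey is not among them.

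The design is randomised, with 35 HFs per arm in each country. According to Allocation and blinding, the selected HFs "were provided with the intervention shortly after completing the baseline data collection".

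The Sample size calculations section says that the same regression models were used to simulate power. For each country it states that "we require the probability of α, a type I error (rejecting the null hypothesis when it is actually true) to be less 0.05", and it asks for "the power to be at least 80" per cent.

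**The concern.** Under randomisation, with a baseline taken before the intervention, any baseline difference between the arms is chance. A difference in change estimates that difference freely and removes all of it. This adds the baseline sampling error to the effect estimate, and it over-corrects a chance imbalance whenever the HF means at the two surveys are less than perfectly correlated. A model that gives both arms one baseline mean removes only the part that the correlation supports.

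Precision on the primary outcomes is at stake. With 35 HFs per arm already fixed, the analysis model is one of the few remaining ways to gain power.

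**Working it through.** **Inputs (Sample size calculations).** J = 35 HFs per arm.
- Diagnostic scope: 30% to 35%, 60 records per HF, k = 0.25.
- Treatment appropriateness: 50% to 60%, 25 children, k = 0.25.
- Vaccination adherence: 75% to 85%, 30 children, k = 0.25.
- Data concordance: ratio 0.7 to 0.8, 100 records, between-HF SD 0.25.

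**Assumptions added here.** Two-sided 5% test (z = 1.96) and a normal approximation on HF means. One dose per child for vaccination. Poisson or binomial within-HF variance for concordance. A correlation c between an HF's true levels at the two surveys, which the article does not give; c = 1, 0.8 and 0.5 are shown.

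**Formulas.** Let b be the between-HF variance, w the within-HF variance of an HF mean, s² = b + w, and r = c·b/s².
- Difference in change: Var = 4(1−r)s²/J.
- Common baseline (end-line difference minus r times baseline difference): Var = 2(1−r²)s²/J.
- Ratio = (1+r)/2, so the reduction is (1−r)/2.
- End-line only: Var = 2s²/J. Difference in change is worse than this when 4(1−r) > 2, that is, r < 0.5.

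**The stated 80% first.** At c = 1, the planned estimator gives power of 0.96 (vaccination), 0.94 (concordance, Poisson; about 1.00 binomial), 0.705 (diagnostic scope) and 0.84 (treatment). No single variant tried gave 80% for all four outcomes.

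**Diagnostic scope, c = 1.**
- b = (0.25×0.30)² = 0.005625; w = 0.30×0.70/60 = 0.0035; s² = 0.009125; r = 0.616.
- Planned: Var = 4×0.0035/35 = 0.00040, SE 0.0200, power Φ(0.05/0.0200 − 1.96) = Φ(0.54) = 0.705.
- Common baseline: Var = 2×(1−0.380)×0.009125/35 = 0.000323, SE 0.0180, power 0.794.
- The ratio of 0.81 is worth 1/0.81 = 1.23 times as many HFs, or about 43 rather than 35 per arm.

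**Treatment appropriateness, c = 1.**
- b = (0.25×0.50)² = 0.015625; w = 0.25/25 = 0.01; r = 0.610.
- SE 0.0338 against 0.0303; power 0.841 against 0.909.

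**Variance reduction (1−r)/2:**

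| Outcome | c = 1 | c = 0.8 | c = 0.5 |
|---|---|---|---|
| Diagnostic scope | 19.2% | 25.3% | 34.6% |
| Treatment appropriateness | 19.5% | 25.6% | 34.8% |
| Vaccination (one dose per child) | 7.5% | 16.0% | 28.8% |
| Data concordance (binomial to Poisson) | 1.6-5.0% | 11.3-14.0% | 25.8-27.5% |

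With 4 to 12 doses per child, the vaccination reduction at c = 1 lies between 1.5% and 7.5%, depending on the within-child correlation.

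**Power, planned / common baseline / end-line only:**

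| Outcome | c = 1 | c = 0.8 | c = 0.5 |
|---|---|---|---|
| Diagnostic scope | 0.705 / 0.794 / 0.591 | 0.585 / 0.711 / 0.591 | 0.461 / 0.634 / 0.591 |
| Treatment appropriateness | 0.841 / 0.909 / 0.743 | 0.733 / 0.849 / 0.743 | 0.601 / 0.783 / 0.743 |
| Vaccination | 0.963 / 0.973 / 0.538 | 0.728 / 0.800 / 0.538 | 0.483 / 0.622 / 0.538 |

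The planned estimator falls behind end-line only when c is below 0.5/0.616 = 0.81 (diagnostic scope), 0.5/0.610 = 0.82 (treatment) or 0.5/0.849 = 0.59 (vaccination).

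**Check by simulation.** Logistic mixed models with an HF random intercept were fitted to 300 simulated trials per scenario, with and without the baseline arm term. The empirical variance reductions were 18% (c = 1) and 34% (c = 0.5) for diagnostic scope, 24% and 32% for treatment, and 4.5% (c = 1) for vaccination. At c = 0.5 the model standard errors were 17-24% too small under both analyses, because a random intercept alone ignores HF changes between surveys.

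**The case against.** The planned interaction is a legitimate, unbiased estimator with a clearly stated question, and the article says that power was simulated with the same models. This stands: nothing is contradicted.

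A reader might go further and infer that the plan wastes its baseline. The figures do not support that. For vaccination with stable HFs, the planned model has power of 0.96 against 0.54 for end-line only, because it removes the stable differences between HFs.

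A reader might also take a gain of about a third as established. That needs c near 0.5, which the article does not state, and it also calls k unknown. Solving instead for the r that gives the stated 80% under difference in change yields 0.70 (diagnostic scope), 0.57 (treatment), 0.73 (vaccination) and 0.84 (concordance). The corresponding reductions are about 15%, 22%, 13% and 8%.

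Nor does the roughly 70% for diagnostic scope show that the stated power is wrong. The simulation code is in supplements not shown, and the calculation here is a linear approximation to models that will be logistic or possibly Poisson.

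The gain also depends on the covariance structure. If HFs drift (c = 0.5) but the baseline is weighted as though they were stable, the vaccination reduction is about 13% rather than 29%.

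Finally, the sentence "If large imbalances are observed at baseline, the variables can be used to adjust the effect estimate comparisons" might be read as a fallback for this issue or as a defect of its own. It concerns population and facility characteristics rather than the baseline value of the outcome, and a named covariate list is commonly left to a statistical analysis plan. No point is made of it.

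**Conclusion.** This is a free improvement to an unbiased analysis, not the correction of an error. On the article's inputs with fully stable HFs, it is worthwhile for diagnostic scope and treatment appropriateness, where the variance falls by about a fifth. It is small for vaccination and data concordance. All the gains grow if true HF levels shift between surveys.

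The conclusion rests on randomisation, on a baseline unaffected by the intervention, on a correctly specified covariance and on the assumed c. It does not apply to health worker satisfaction in Nigeria, which is measured at end-line only, or to household vaccination adherence in Mozambique, where the household survey was cancelled.

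**What to change.** For each outcome with a baseline, fit survey plus an arm-at-end-line term with no baseline arm term, and include both HF and HF-by-survey random effects. The HF-by-survey effect is needed for valid standard errors under the planned interaction as well. An alternative is to analyse end-line adjusted for the HF's baseline value of the same outcome. For logistic or Poisson mixed models this is a related analysis, not an identical one, so one of the two should be named as primary. Keep the plain interaction as a sensitivity analysis.

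The cost is a sentence in the analysis text, one term removed and one random effect added, with no further data. The article has analysts blinded until the code is final, so the choice can be made without knowledge of results, provided it is recorded before the arms are disclosed.

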For the outcome related to HWs’ satisfaction, we would be able to detect as significant an increase from 50% of HWs satisfied to 75%, with 80% power assuming 35 HF, three HWs per HF and a variation between HF equivalent to k=0.25. Since this variable is measured in the end-line survey only, we used the formula in Hayes and Bennett.^20^

In summary, in each country we require 35 HF per arm, 3 HW per HF, 100 vaccination records per HF, 60 sick child records per health facility and 30 children per health facility catchment area.

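### The sections disagree on where health worker satisfaction has a baseline, so the contrast for this primary outcome outside Nigeria is not consistently stated; if it is the arm-by-survey interaction, the power calculation does not cover it

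*Protocol article*

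**What the plan says.** Four statements in the Protocol article bear on this outcome.

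- Outcomes: "There are five primary outcomes (table 2"). Health worker satisfaction is the fifth row of Table 2.
- Sample size calculations: satisfaction is powered for "an increase from 50% of HWs satisfied to 75%, with 80% power". The inputs are 35 facilities with three workers in each, and k = 0.25 for the spread between facilities. A closed formula replaces the two-survey simulation, for this reason: "Since this variable is measured in the end-line survey only". No country is named, and the summary applies the sizes to each country: "in each country we require 35 HF per arm, 3 HW per HF".
- Data analysis: "Four of the primary outcomes are measured at baseline and end-line". Their effect is the interaction between arm and survey.
- Data analysis, same paragraph: "The effect of HW satisfaction in Nigeria, measured only at end-line, will be estimated as the difference between the intervention and control arms".

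Each country is analysed separately, and each must reach at least 80% power at a type I error below 0.05.

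**The concern.** The Sample size section and the count of four outcomes with a baseline both imply that satisfaction has no baseline anywhere. The Nigeria sentence implies that end-line-only measurement is particular to Nigeria, and so that a baseline exists in the other two countries.

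- If satisfaction is end-line only everywhere, the words limiting this to Nigeria are wrong, and they leave two countries without a stated contrast.
- If it is end-line only in Nigeria alone, the Sample size statement is wrong, and the count of four is wrong for the other two countries.

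The estimator for a primary outcome then has to be guessed in two of three countries. The choice matters because the plan's rule for outcomes with a baseline is a difference in differences. With about three workers per facility, subtracting a noisy baseline mean from a noisy end-line mean can cost precision that the end-line-only calculation never allowed for.

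**Working it through.** **Inputs from the Sample size section.** p0 = 0.50, p1 = 0.75, m = 3 workers per facility, k = 0.25, 35 facilities per arm, alpha 0.05 (taken as two-sided; the article does not say).

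**Assumptions not in the article.** ρ is the correlation of facility effects between surveys (0 to 1). r is the correlation of a worker's own responses between surveys (0 for different or uncorrelated workers). Both arms start at 50%.

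**Step 1: the plan's own figure (end-line difference).** The usual formula for unmatched clusters is c = 1 + (1.96 + 0.84)² V / (p1 − p0)², with V = p0(1−p0)/m + p1(1−p1)/m + k²(p0² + p1²).

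- V = 0.0833 + 0.0625 + 0.0156 + 0.0352 = 0.1966.
- For 80% power, c = 25.7, so 26 facilities per arm.
- With 35 per arm: √(34 × 0.0625 / 0.1966) = 3.29; power = Φ(3.29 − 1.96) = 91%. Simulation also gives about 91%.

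The stated 80% is therefore a floor that is met with some reserve. Reading 35 as the total over both arms would give 63%, but the section's summary says 35 per arm.

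**Step 2: arm-by-survey interaction on the same inputs.** The variance per facility pair is W + B:

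- W = [0.25 + 0.25 − 2r(0.25)]/3 + [0.25 + 0.1875 − 2r√(0.25 × 0.1875)]/3
- B = k²[0.5² + 0.5² − 2ρ(0.5)(0.5)] + k²[0.5² + 0.75² − 2ρ(0.5)(0.75)]

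With r = 0, W = 0.3125.

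- ρ = 0: B = 0.0820, total 0.3945. Power is 64% using 34 (keeping the formula's +1) or 65% using 35.
- ρ = 1: B = 0.0039, total 0.3164. Power is 74% or 75%.

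About 41 to 51 facilities per arm would be needed for 80%. Simulation gives 65% and 75%. A logit-scale approximation with stable facility effects gives 77%.

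**Step 3: let the same workers answer twice.** Interaction power, keeping the +1:

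| r | ρ = 0 | ρ = 0.5 | ρ = 0.8 | ρ = 1 |
|---|---|---|---|---|
| 0 | 64% | 69% | 72% | 74% |
| 0.2 | 72% | 77% | 80% | 82% |
| 0.3 | 76% | 81% | 85% | 87% |
| 0.4 | 80% | 86% | 89% | 91% |
| 0.5 | 85% | 90% | 93% | 95% |

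The 80% line is crossed at r of about 0.15–0.2 with stable facility effects and about 0.4 with unstable ones.

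**Step 4: end-line difference adjusted for the facility's baseline mean.** With b the pooled slope, v₀ = 0.0833 + 0.0156 = 0.0990 the variance of a baseline facility mean, and C the baseline–end-line covariance summed over the two arms, the variance is 0.1966 + 2b²v₀ − 2bC, where b = C/(2v₀).

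- Example, ρ = 0.8 and r = 0.2: C = 0.0292 + 0.0332 = 0.0624; b = 0.315; variance = 0.1966 + 0.0196 − 0.0393 = 0.1770; power 93%, against 80% for the interaction.
- Over ρ from 0 to 1 and r from 0 to 0.5, power is 91% to 98%, above the interaction in every case tried.

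**The case against.** A reader might infer that the plan applies the interaction to satisfaction in Côte d'Ivoire and Mozambique, and that it would therefore miss its 80% power. The article supports neither step.

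- **The interaction is never assigned to this outcome.** It goes to four primary outcomes, and satisfaction is the one left over. Two of the three statements on timing point to an end-line comparison. No section says that a satisfaction baseline was collected in those two countries, and the Nigeria wording may be a drafting slip.
- **The shortfall rests on independent responses.** The article surveys all workers in each included facility and excludes facilities planning staff turnover, so many of the same people could plausibly answer both surveys. A modest within-worker correlation removes the shortfall.
- **The scale may differ.** Table 2 defines satisfaction as a score, and the analysis leaves its model to the distribution. Power for a 50% v 75% dichotomy need not carry over to a score.
- **Different estimators by country do limited harm**, since countries are analysed separately and no pooled estimate is described.
- **The interaction is a legitimate estimator**, and model detail can be left to an analysis plan.

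The first three points stand, and they limit the power statement to a conditional one. The fourth also stands, so the argument here does not rest on it. The last stands only in part. The article does not leave the contrast for this outcome open: it states one, inconsistently. And the baseline-adjusted contrast does better than the interaction even when repeat responses bring the interaction back above 80%.

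**Conclusion.** The contradiction holds from the text alone and needs no assumption: the contrast for a primary outcome in two of the three countries is not consistently stated.

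The loss of power is conditional. It arises only if a baseline exists outside Nigeria and the interaction is used there. Power could then fall from about 91% to about 64–75% with independent responses, a loss of roughly 16 to 27 percentage points; it would be 80% or more once within-worker correlation reaches about 0.2 to 0.4, depending on how stable facility effects are. These figures assume a binary outcome, a two-sided test and equal baselines in the arms. The article gives neither correlation, so it cannot be said that the trial misses its target. What can be said is that the satisfaction calculation does not cover an interaction. The point is worth correcting because the outcome is primary and the change is cheap.

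**What to change.** 1. In Sample size calculations and Data analysis, state the same thing about which countries have a baseline measurement of satisfaction, and make the count of outcomes with a baseline agree with it.
2. In Data analysis, estimate satisfaction in every country as the end-line difference between arms with a facility random effect. Where a baseline exists, add the facility's baseline mean as a covariate instead of using the arm-by-survey interaction. The target contrast is then the same in all three countries, and the end-line power calculation remains a fair, slightly conservative, basis for it.

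This costs a few sentences of analysis wording, with no new data and no change in sample size. The article places end-line data collection ahead, so the choice can be fixed before those data are seen.
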